### Study population

Patients aged ≥70 years with ECOG performance status of 0–2, who have cytologically or histologically confirmed previously untreated unresectable mCRC are eligible. *RAS* (*KRAS* exon 2,3 and 4; *NRAS* exon 2 and 3) wildtype, *BRAF* wildtype or non-*V600E BRAF* mutations, as assessed by a local laboratory, are eligible. Other main eligibility criteria include:
Measurable disease according to RECIST 1.1.No prior chemotherapy, except for adjuvant chemotherapy given in association with (i) complete resection of primary colon or rectal cancer provided there is no clinical, radiological or biochemical evidence of relapse for at least 6 months after completion of adjuvant treatment and/or (ii) complete resection of limited colorectal metastases to liver and/or lung provided there is no clinical, radiological or biochemical evidence of relapse for at least 6 months after completion of adjuvant treatment.Prior palliative radiotherapy is allowed, provided at least 2 weeks after completion of therapy has elapsed before enrolment, any toxicities have resolved to grade 1 or less.
Prior fluoropyrimidine chemotherapy, concurrent with radiation as neoadjuvant treatment for rectal cancer is allowed.Prior radiotherapy, concurrent with radiation sensitising fluoropyrimidines in the setting of metastatic disease is allowed.Adequate organ function defined as follows:Bone marrow: ANC (absolute neutrophil count) > 1500/μl, platelets > 75,000/μl, haemoglobin > 8 g/dl. INR (international normalised ratio) and APTT (activated partial thromboplastin time) < 1.5 x ULN (upper limit of normal). Note: patients previously on long-term anticoagulation with warfarin or low molecular weight heparin are eligible.Adequate liver function: Albumin > 25 g/l; Total bilirubin < 3 x ULN; AST (aspartate transaminase), ALT (alanine transaminase) and/or ALP (alkaline phosphatase) < 5 x ULN.Adequate renal function, creatinine clearance, as measured by the Cockcroft and Gault formula of >30mls/minute.Serum potassium, magnesium and total calcium <grade 2 above or below the institution’s normal limits. Note: total calcium should be corrected for albumin level as per the institution’s usual calculation method.Patient is being treated with non-curative intent. This may be because the disease is anatomically not resectable, that resection is contraindicated for any reason, or the patient refuses resection.

Main exclusion criteria include:
History of interstitial lung disease or pulmonary fibrosis.Prior exposure to cetuximab, panitumumab or bevacizumab.Contraindication to study medications.Leptomeningeal disease as the only manifestation of their malignancy.Untreated/active CNS metastases; i.e. progressing, requiring ongoing corticosteroids or anticonvulsants for symptom control. Patients with CNS metastases are eligible if previously successfully treated with surgery and or radiotherapy at least 8 weeks prior to Cycle 1 Day 1, are off all corticosteroids and/or anticonvulsants for at least 4 weeks and imaging within 4 weeks of Cycle 1 Day 1 excludes any progression.Life expectancy of less than 3 months.

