**Methods/design:**

MONARCC is a prospective, open-label, multicentre, non-comparative randomised phase II trial. Eligible patients aged ≥70 with unresectable metastatic, untreated, *RAS*/*BRAF* wildtype metastatic colorectal cancer will be randomised 1:1 to receive panitumumab alone or panitumumab plus infusional 5-fluorouracil. *RAS* and *BRAF* analyses will be performed in local laboratories. Comprehensive Health Assessment and Limited Health Assessments will be performed at baseline and at 16 weeks, respectively, to assess frailty. The Patient Symptom Questionnaire and Overall Treatment Utility are to be undertaken at different timepoints to assess the impact of treatment-related toxicities and quality of life. Treatment will be delivered every 2 weeks until disease progression, unacceptable toxicity (as determined by treating clinician or patient), delay of treatment of more than 6 weeks, or withdrawal of consent. The primary end point is 6-month progression-free survival in both arms. Secondary end points include overall survival, time to treatment failure, objective tumour response rate as defined by RECIST v1.1 and safety (adverse events). Tertiary and correlative endpoints include the feasibility and utility of a comprehensive geriatric assessment, quality of life and biological substudies.

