## Background

Doublet chemotherapy (e.g., FOLFOX or FOLFIRI) in combination with a biologic agent (anti-EGFR or anti-VEGF) are established first-line treatments against metastatic colorectal cancer (mCRC) [1, 2]. In patients with *KRAS* exon 2 wildtype mCRC, the use of anti-EGFR antibodies with doublet chemotherapy in the first-line setting has demonstrated superior overall survival (OS) compared with bevacizumab with doublet chemotherapy or doublet chemotherapy alone [1–3]. Subsequent studies have established the benefit of adding anti-EGFR antibodies to first-line doublet therapies is also limited to tumours without mutations in other RAS exons [4, 5]. Therefore, anti-EGFR antibodies are only indicated in patients with no *KRAS* or *NRAS* mutations in exons 2, 3 or 4, which accounts for approximately 40–50% of cases of mCRC. In addition, in patients with *RAS* wildtype disease, the benefit derived from anti-EGFR antibodies is far greater in left-sided than right-sided primary tumours [6, 7]. Approximately 10% of mCRC harbour activating mutations in *BRAF V600E* which are mutually exclusive with *RAS* mutations [8]. Anti-EGFR antibodies have limited, if any activity against *BRAF V600E* mutant cancers, unless combined with a *BRAF* inhibiting agent [9–11]. Therefore, easily determined predictive biomarkers exist to enable selection of patients for treatment with anti-EGFR antibodies.

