### Design

*MONARCC* is a prospective, non-comparative randomised phase II, open-label multicentre clinical trial in which patients with histologically confirmed *RAS* and *BRAF* wildtype untreated metastatic colorectal adenocarcinoma are randomised 1:1 ratio to either panitumumab monotherapy (Arm A) or panitumumab plus infusional 5-FU as per the De-Gramont schedule (Arm B). All treatments are to be administered until disease progression, unacceptable toxicity (as determined by treating clinician or patient), treatment delays of longer than 6 weeks, or withdrawal of consent (Fig. 1). Randomisation will be performed centrally using the method of minimisation where patients will be stratified on performance status (Eastern Cooperative Oncology Group [ECOG] 0, 1 vs 2), site of primary tumour (left vs right), number of metastatic sites (1 vs > 1) and treating institution. Left-sided tumour is defined as at, or distal to, the splenic flexure. All patient will receive doxycycline or minocycline 50–100 mg once a day commencing on Cycle 1 Day 1 for a minimum of 6 weeks as a pro-active approach in managing skin toxicity from panitumumab. MONARCC incorporates a number of patient questionnaires and a Comprehensive Health Assessment (CHA) is conducted at baseline. During therapy, patients complete symptom Patient Symptom Questionnaire (PSQ) and Limited Health Assessment Questionnaire (LHA). Overall Treatment Utility (OTU) is also evaluated. This is a novel endpoint using a composite of clinical and radiological response, toxicity, adverse events and patient response when asked to reflect if treatment has been worthwhile. CHA, LHA, PSQ and OTU were originally developed and used in the MRC FOCUS2 study, based on validated and published questionnaires (Additional file 1) [24]. A list of participating centres is provided in Table 2.

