### Translational analyses

In addition to addressing the clinical questions, the trial also incorporates translational analysis. Archival formalin-fixed paraffin-embedded (FFPE) tissue collection, which is mandatory for study entry, will be used for central review of *RAS*/*BRAF* mutation status and for translational studies. Blood collection are required of all patients for translational endpoints and will be collected at three timepoints: Cycle 1 Day 1, Cycle 3 Day 1 and at 24 weeks. Blood, serum, plasma and tumour specimens will be biobanked. The program will investigate a number of biomarkers identified a priori, which focus on both discovery/ hypothesis generation and validation objectives. No additional tumour samples, other than those obtained for clinical purposes, will be requested.

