### Statistical considerations

The primary endpoint, PFS at 6 months in each treatment arm, will be assessed to determine if these protocols are reasonable alternatives to current standard therapy of capecitabine and bevacizumab. The expected PFS rate is approximately 73% in *RAS*/*BRAF* wildtype tumours in prior studies of capecitabine and bevacizumab. Using the method of Mehta-Cain, a total planned sample size of 80 patients, with 40 patients in each group, would include the upper 95% one-sided confidence interval for the proportion of patients who have not progressed at 6 months, including 73% if more than 23 patients are progression-free at 6 months in either group.

The analysis of PFS at 6 months and OS will be estimated using the method of Kaplan-Meier. Analysis of efficacy endpoints will be undertaken in the final analysis, and there is no planned interim analysis.

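### The entry criterion leaves NRAS exon 4 out of the RAS definition, against the article's own Background, and admits non-V600E BRAF mutations under an unqualified BRAF wildtype label

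*Protocol article*

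**What the plan says.** All references are to the protocol article.

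- **Study population** gives the operative criterion: "RAS* (*KRAS* exon 2,3 and 4; *NRAS* exon 2 and 3) wildtype, *BRAF* wildtype or non-*V600E BRAF* mutations, as assessed by a local laboratory, are" accepted for entry. KRAS is covered in exons 2, 3 and 4, NRAS in exons 2 and 3.
- **Background**, first paragraph, states the indication: "anti-EGFR antibodies are only indicated in patients with no *KRAS* or *NRAS* mutations in exons 2, 3 or 4". On BRAF it says: "Anti-EGFR antibodies have limited, if any activity against *BRAF V600E* mutant cancers", with an exception for combination with a BRAF inhibitor. It says nothing about other BRAF mutations.
- **Abstract, Methods/design** describes the patients as "untreated, *RAS*/*BRAF* wildtype metastatic colorectal cancer will be randomised 1:1". **Design** says that "patients with histologically confirmed *RAS* and *BRAF* wildtype untreated metastatic colorectal adenocarcinoma are randomised 1:1 ratio". The closing paragraph of the Background uses the same label. None of the three qualifies it.
- **Statistical considerations** takes its reference rate from the same label: "The expected PFS rate is approximately 73% in *RAS*/*BRAF* wildtype tumours in prior studies of capecitabine and bevacizumab". It plans 40 patients per arm and a threshold of more than 23 progression-free at 6 months.
- **Translational analyses** states that archival tissue "will be used for central review of *RAS*/*BRAF* mutation status and for translational studies".

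**The concern.** The entry criterion is the sentence that decides who may be randomised, and it is wider than the indication that the same article states. The two differ by exactly one item, NRAS exon 4. A tumour with a known mutation there passes the printed criterion, although by the Background the drug class is not indicated for it. In Arm A (Study procedures) that patient would receive panitumumab with no other anticancer drug.

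The BRAF part is a separate and lesser matter. The criterion openly admits non-V600E mutations, while the trial is described elsewhere as enrolling BRAF wildtype disease. A conclusion worded for RAS/BRAF wildtype patients would then cover some who are not.

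What is at stake is the exposure of a small group whom the document itself places outside the indication, and the accuracy of the population statement attached to the result.

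**Working it through.** **1. The passages side by side**

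| Item | Background | Study population | Agreement |
|---|---|---|---|
| KRAS exons 2, 3, 4 | must be unmutated | must be unmutated | yes |
| NRAS exons 2, 3 | must be unmutated | must be unmutated | yes |
| NRAS exon 4 | must be unmutated | not listed | **no** |
| BRAF V600E | little or no activity | not eligible | yes |
| BRAF non-V600E | no statement | eligible | no conflict |

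The last row does conflict with the label: the Abstract, the closing paragraph of the Background and the Design section say BRAF wildtype without exception.

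**2. Does another criterion close the NRAS gap?** None of the listed exclusions names RAS status. The nearest is the general exclusion for a contraindication to study drugs. The article does not say that it covers a RAS mutation, and RAS eligibility has its own explicit exon list. The gap is not clearly closed.

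**3. The plan's decision rule.** Inputs from Statistical considerations: n = 40 per arm, one-sided 95% upper limit, reference 73%. The exact (Clopper-Pearson) upper limit for x successes is the 0.95 quantile of Beta(x + 1, n − x).

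- x = 23: 0.708, which excludes 0.73.
- x = 24: 0.731, which includes 0.73.

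The stated threshold of more than 23, that is at least 24 of 40, is reproduced. The point raised here does not alter it.

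**4. How far could the admitted tumours move the result?** The documents give neither their share f nor their 6-month PFS rate q, so both are assumptions. With a rate b in fully wildtype patients, the arm's overall rate is m = (1 − f) × b + f × q, and the chance of passing is P(X ≥ 24) for X ~ Binomial(40, m).

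With b = 0.73 and f = 0 the chance is 0.975. Otherwise:

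| f | patients per arm (f × 40) | m, q = 0 to 0.5 | P(X ≥ 24) |
|---|---|---|---|
| 1% | 0.4 | 0.723 to 0.728 | 0.968 to 0.973 |
| 3% | 1.2 | 0.708 to 0.723 | 0.950 to 0.969 |
| 5% | 2 | 0.694 to 0.719 | 0.924 to 0.964 |
| 10% | 4 | 0.657 to 0.707 | 0.823 to 0.948 |

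Example: f = 5% and q = 0 give m = 0.95 × 0.73 = 0.6935.

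The rule is more sensitive if the true rate lies near the threshold proportion, 24/40 = 0.60. With b = 0.60 the chance of passing is 0.568 when f = 0, 0.537 to 0.563 when f = 1%, and 0.415 to 0.543 when f = 5%. That reflects the steepness of any 40-patient rule near its cut-off. It is not evidence that these tumours are frequent or do badly.

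**The case against.** The strongest reply is that this is a journal article. Sites work from the full protocol (v2.0 is named under Ethics), the article lists only the main criteria, and the missing exon may be a slip in condensing. The Background shows that the authors knew the full exon set. This stands as a limit: it cannot be said from the article that sites are enrolling such patients. It does not remove the discrepancy, because the article does not leave the exon list to another document. It prints one, and that list disagrees with its own Background.

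A second reply is that RAS/BRAF wildtype is shorthand which the eligibility section then defines. That is fair, and it reduces the BRAF part to a question of labelling.

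A reader might infer four stronger points. The documents do not support them.

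- *That the Background calls the drug not indicated for the admitted BRAF-mutant patients.* Its indication sentence concerns KRAS and NRAS, and its BRAF statement stops at V600E.
- *That the 73% benchmark excludes tumours this trial admits.* The article does not say which exons or BRAF variants the prior studies tested, so a mismatch cannot be shown.
- *That these patients are predictable failures who could reverse an arm's verdict.* No outcome is given for either group. One or two patients of any kind can decide an arm that sits at the threshold.
- *That central review lacks a role in the primary analysis.* Such a role is commonly left to the full protocol or SAP, which are not shown, so its absence here is not an error.

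**Conclusion.** The point holds in a limited form. On NRAS exon 4 the entry criterion and the stated indication contradict each other as printed, and no listed exclusion clearly resolves this. On BRAF, the criterion and the population label do not match, but the criterion does not contradict the Background.

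The numerical effect is probably small. If the wildtype 6-month PFS rate is 73%, and 1% to 5% of patients carry the admitted mutations with a 6-month rate anywhere from 0 to 50%, the chance of passing falls by 0.002 to 0.051 from 0.975. These shares and rates are assumptions. Larger effects need a share near 10% or a true rate close to 60%. If the admitted patients do worse, the error makes an arm less likely to pass, so it does not favour the study regimens.

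The reasons to act are patient exposure and the wording of the conclusion. The Discussion reports 28 patients accrued in November 2020 against 80 planned. At that date 80 − 28 = 52 patients remained to be enrolled under whichever list the full protocol contains.

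**What to change.** 1. Check the exon list in the full protocol. If it includes NRAS exon 4, correct the article. If it does not, reconcile the eligibility section with the Background by amendment, so that the entry criterion and the stated indication agree.
2. Describe the enrolled population in the abstract, the design section and the eventual conclusions by the BRAF criterion actually applied, for example as BRAF V600E-negative.

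The cost is one check of the protocol, at most a one-line amendment to the criterion, and an edit to the population description. If entry were narrowed as a result, some candidates would be lost to a trial that is already recruiting slowly. The documents do not allow that number to be estimated.

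Optional, and not part of the error: keep all randomised patients in the primary analysis, and add a sensitivity analysis of 6-month PFS in those confirmed RAS/BRAF wildtype by the central review already planned.

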### Study procedures

All patients will complete the CHA questionnaire at baseline. Patients enrolled in Arm A and Arm B will receive panitumumab monotherapy 6 mg/kg IV and panitumumab 6 mg/kg IV plus infusional 5-FU (5-FU bolus 400 mg/m^2^, leucovorin 200 mg/m^2^, 5-FU 46-h infusion at 2400 mg/m^2^), respectively. Treatment is delivered every 2 weeks until disease progression, unacceptable toxicities, treatment delay of more than 6 weeks, or withdrawal of consent. For patients needing to cease 5-FU in Arm B, the continuation of panitumumab alone is permitted. Switching the route of administration of 5-FU; e.g., to oral capecitabine, during the study is not permitted. All patients will receive doxycycline or minocycline at 50–100 mg once a day commencing on Cycle 1 Day 1. This will continue for a minimum of 6 weeks but could be continued for longer as deemed appropriate by the investigator. Disease assessment by CT or MRI scan will be performed every 8 weeks until disease progression. The PSQ will be completed every 4 weeks until disease progression. The OTU is to be scored at Weeks 8 and 16 from the PSQ/LHA, with the LHA to be completed once at 16 weeks. Serum CEA is to be assessed every 4 weeks until disease progression.

### Translational analyses

In addition to addressing the clinical questions, the trial also incorporates translational analysis. Archival formalin-fixed paraffin-embedded (FFPE) tissue collection, which is mandatory for study entry, will be used for central review of *RAS*/*BRAF* mutation status and for translational studies. Blood collection are required of all patients for translational endpoints and will be collected at three timepoints: Cycle 1 Day 1, Cycle 3 Day 1 and at 24 weeks. Blood, serum, plasma and tumour specimens will be biobanked. The program will investigate a number of biomarkers identified a priori, which focus on both discovery/ hypothesis generation and validation objectives. No additional tumour samples, other than those obtained for clinical purposes, will be requested.

### Statistical considerations

The primary endpoint, PFS at 6 months in each treatment arm, will be assessed to determine if these protocols are reasonable alternatives to current standard therapy of capecitabine and bevacizumab. The expected PFS rate is approximately 73% in *RAS*/*BRAF* wildtype tumours in prior studies of capecitabine and bevacizumab. Using the method of Mehta-Cain, a total planned sample size of 80 patients, with 40 patients in each group, would include the upper 95% one-sided confidence interval for the proportion of patients who have not progressed at 6 months, including 73% if more than 23 patients are progression-free at 6 months in either group.

The analysis of PFS at 6 months and OS will be estimated using the method of Kaplan-Meier. Analysis of efficacy endpoints will be undertaken in the final analysis, and there is no planned interim analysis.

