Most recently, the PANDA study was presented in abstract form. This phase 2 study randomised 185 patients aged ≥70 years with untreated wildtype *RAS* and *BRAF* mCRC to receive FOLFOX plus panitumumab or 5-fluorouracil (5-FU) plus panitumumab. The median age of 77 years in both arms is similar to that in other studies investigating an elderly population. The geriatric assessment G8 score was prospectively collected and used as a stratification factor. The primary endpoint of PFS was reached in each arm, at 9.6 months (95% CI 8.8–10.9, *p* < 0.001) and 9.1 months (95% CI 7.7–9.9, *p* < 0.001) in the FOLFOX-panitumumab and the 5-FU-panitumumab arms, respectively. The overall response rate and disease control rate were similar, and the 5-FU plus panitumumab arm had a lower incidence of toxicities. The results demonstrated panitumumab plus mono-chemotherapy is clinically active and well tolerated. However, as chemotherapy was used in both treatment arms, the efficacy of panitumumab monotherapy could not be evaluated [21]. Taken together, these data support further investigation of anti-EGFR antibodies as components of less intensive treatment regimens for elderly patients with untreated *RAS* and *BRAF* wildtype mCRC. A summary of selected studies investigating anti-EGFR antibodies in elderly patients with untreated mCRC is presented in Table 1.

**Table 1 Tab1:** Selected studies involving anti-EGFR antibodies in elderly patients with mCRC

Study	Design	Population	Treatment	Sample size	Primary endpoint	Key Results
Sastre, 2011 [18]	Prospective single arm, phase II.	Patients aged ≥70 with unselected mCRC	Cetuximab monotherapy	41	Overall response rate (ORR)	ORR 14.6% (95% CI 5.6–29.2)
Sastre, 2012 [20]	Prospective, Single arm, phase II	Patients aged ≥70 with unselected mCRC	Cetuximab plus capecitabine	66	Overall response rate (ORR)	ORR 31.8% (95% CI 20.9–44.4) 29 patients had KRAS wild-type disease: response rate 48.3% (95% CI 29.4–67.5),
Sastre, 2015 [19]	Prospective, Single arm, phase II	Patients aged ≥70 with RAS wild-type mCRC	Panitumumab monotherapy	33	PFS at 6 months	6-month PFS rate 36.4% (95% CI 20.0–52.8)
Kinele, 2018 [22]	Prospective, open label randomised phase II	Patients > 75 years, or patients ≥70 years with at least one adverse factor	Cetuximab monotherapy; cetuximab plus capecitabine	24	PFS at 12 weeks	PFS at 12 weeks: monotherapy arm 55% (95% CI 23–83); combination arm 69%; 95% CI 39–91)

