## Discussion

MONARCC addresses a clinically important question in a prevalent, but under-investigated population that will help inform future practice in elderly patients with *RAS*/*BRAF* wildtype mCRC. Similar to the PANDA trial, MONARCC also incorporates geriatric assessment by prospectively collecting Comprehensive Health and Limited Health Assessment questionnaires, together with physical activity levels measured by activity tracking devices. These aspects of cancer treatment remain under-researched and will add value to the study.

Since the inception of MONARCC in early 2018, other clinical trials have shed light on the use of anti-EGFRs in the elderly population. SAAK 41/10 was a prospective randomised phase II study that evaluated cetuximab monotherapy and cetuximab plus capecitabine as first-line treatment in extended RAS wildtype mCRC; however, the trial was stopped prematurely due to slow accrual. Within the limitations of the small sample size, the authors concluded that upfront cetuximab appeared tolerable and showed promising activity in left-sided tumours [25].

MONARCC is the first study to evaluate the activity of panitumumab monotherapy and panitumumab plus infusional 5-FU in this population. Current accrual (as at 20 November 2020) is 28 patients from 21 sites across Australia. Despite the significance of the clinical question, the recruitment rate of MONARCC has been lower than expected. Challenges to recruitment include a high frequency of *RAS*/*BRAF* mutations, alternative treatment preference such as surgery, multi-agent or oral chemotherapy, and the impact of the COVID-19 pandemic. Strategies to overcome these challenges include setting up tele-trial and satellite sites to expand the study’s reach.

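### Reaching 24 of 40 shows only that 73% has not been excluded, which is too little to call a regimen a reasonable alternative to a 73% standard

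*Protocol article*

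**What the plan says.** All of this is in the Statistical considerations section of the protocol article.

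- **Purpose.** 6-month PFS in each arm "will be assessed to determine if these protocols are reasonable alternatives to current standard therapy of capecitabine and bevacizumab".
- **Benchmark.** A 6-month rate of about 73%, taken from prior studies of that standard in *RAS*/*BRAF* wildtype tumours.
- **Size.** "a total planned sample size of 80 patients, with 40 patients in each group", by the Mehta-Cain method.
- **Criterion.** The one-sided 95% upper limit on the 6-month rate must still reach the benchmark. The article puts the count for this as "including 73% if more than 23 patients are progression-free at 6 months in either group".

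The article gives no other criterion for the stated purpose. It names no unacceptable rate, sets no condition on the lower limit, and does not report how likely an arm of a given true rate is to reach the mark.

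**The concern.** The purpose and the criterion do not fit together. To call a regimen a reasonable alternative to a standard, one needs evidence that it is not much worse. The criterion asks instead whether the data have failed to show that the rate is below 73%. With 40 patients the interval is wide, so a rate well below 73% can easily survive that question.

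The error that the rule limits is discarding an arm that truly matches the benchmark. For the stated purpose the reader also needs the chance of accepting an arm that is materially worse, and the article does not give it. If an arm finishes at or just above the mark, the primary conclusion would claim more than the data can carry.

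**Working it through.** **Inputs.** n = 40 per arm, benchmark 73%, one-sided 95% upper limit, and pass at more than 23 (so X ≥ 24), all from Statistical considerations. The true rates from 45% to 70% are chosen here to show the shape of the rule; the article names none of them. The low anchor of 36.4% comes from Table 1 in the Background, for an earlier panitumumab monotherapy study: "6-month PFS rate 36.4% (95% CI 20.0–52.8" (per cent). All patients are taken as evaluable at 6 months.

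**Step 1: reproduce the stated mark.** The exact (Clopper-Pearson) one-sided 95% upper limit for x of n is the 0.95 quantile of Beta(x + 1, n − x).

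- x = 23: Beta(24, 17) gives 70.8%, which excludes 73%.
- x = 24: Beta(25, 16) gives 73.06%, which includes 73%.

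So 24 is the smallest count that does not exclude 73%, and the article's figure is correct. A continuity-corrected Wald limit gives the same mark (71.6% and 74.0%). Uncorrected Wald and Wilson limits would give 25, which does not match the text.

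**Step 2: the error the rule limits.** P(X ≤ 23 | n = 40, p = 0.73) = 1 − 0.975 = 0.025.

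**Step 3: the chance of passing at lower true rates.** P(X ≥ 24) = Σ C(40, k) p^k (1 − p)^(40 − k), for k = 24 to 40.

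| True 6-month PFS | P(arm reaches 24/40) |
|---|---|
| 36.4% | 0.2% |
| 45% | 4.1% |
| 50% | 13% |
| 55% | 32% |
| 60% | 57% |
| 65% | 80% |
| 70% | 94% |
| 73% | 97.5% |

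The probability crosses one half at a true rate of 58.7%.

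**Step 4: what a bare pass shows.** The exact one-sided 95% lower limit is the 0.05 quantile of Beta(x, n − x + 1). At x = 24, Beta(24, 17) gives 45.8%. Read as a test of p ≤ 45%, the same mark has one-sided alpha 4.1% and power 97.5% at 73%.

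**Step 5: would a higher mark cure it?**

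| Rate to be excluded | Mark with n = 40 | Alpha | Power at 73% | P(pass) at 60% |
|---|---|---|---|---|
| 45% | 24 | 4.1% | 97.5% | 57% |
| 50% | 26 (lower limit 50.8%) | 4.0% | 90% | 32% |
| 60% | 30 | 3.5% | 47% | 3.5% |

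Excluding 60% with about 80% power at 73% would take about 85 patients per arm (mark 59, alpha 4.7%, power 81%). With 40 per arm, no mark both excludes 60% and keeps adequate power at 73%.

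**The case against.** The strongest defence is that this is a non-comparative phase II screen. A low chance of discarding a useful regimen is a recognised aim there, and the rule does reject poor regimens: 0.2% pass at the earlier monotherapy rate of 36.4%, and 4.1% at 45%. This stands. A reader might infer that the chance of accepting an inferior arm has no limit at all. That is not so: n and the mark fix it, although the article does not report it.

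The 60% figure is also an illustration. It equals the pass mark (24/40), and any rule passes about half the time when the truth sits at its cut-off. Whether 60% is unacceptable for a lighter regimen in patients aged 70 or over is not settled in the article. This limits how the 57% may be used, but it does not make a pass into evidence of closeness to 73%.

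Two stronger readings are tempting and are not supported.

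- A reader might take the word either to mean that one passing arm makes the trial a success. The abstract, Study endpoints and Statistical considerations all define the endpoint for both arms or for each arm, so the natural sense is whichever arm is being judged.
- A reader might combine slow recruitment ("Current accrual (as at 20 November 2020) is 28 patients from 21 sites across Australia") with the rule and conclude that a smaller trial would pass weaker regimens. The article states a count for 40 per arm only and proposes no early stop. It describes ways to raise accrual.

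Finally, the article condenses a full protocol that is not shown and may name an unacceptable rate. The remark that none is named applies to the article alone.

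**Conclusion.** The point holds as a mismatch between rule and conclusion. The mark is computed correctly and screens out clearly poor regimens. But an arm that just reaches it has excluded only rates below about 46%. An arm 13 percentage points below the benchmark (73 − 60) would pass 57% of the time, and one 8 points below (73 − 65) would pass 80% of the time. A pass therefore cannot, by itself, support calling a regimen a reasonable alternative to a 73% standard.

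This rests on three assumptions:

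- The 24/40 mark is the criterion for the stated purpose. It is the only one given, in the same paragraph, although the article does not use the word success.
- All 40 patients per arm are evaluable at 6 months. The planned Kaplan-Meier estimate would differ from the simple proportion only with censoring before then.
- The limits are exact binomial, which reproduces the stated mark.

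The working does not show that the mark itself must change. Moving it to 26/40 would still pass a 60% arm 32% of the time.

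**What to change.** Keep 40 per arm and the 24/40 mark, and change what is concluded from it:

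1. State that reaching 24/40 in an arm rules out a 6-month PFS rate of 45% or less (one-sided alpha 4.1%, power 97.5% at 73%), and that it is not by itself evidence of a reasonable alternative to a 73% standard.
2. Report the lower as well as the upper one-sided 95% limit for each arm.
3. Give the pass probabilities at true rates from 50% to 65% (13%, 32%, 57% and 80% at 50%, 55%, 60% and 65%).

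This needs wording only and no extra patients. The price is a weaker stated conclusion.

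A stricter mark is optional. If the sponsor wants one, it must name and justify its own unacceptable rate. For example, excluding 50% would need 26/40 (alpha 4.0%), and power at 73% would fall from 97.5% to 90%. That would be a substantive amendment to the primary criterion of an open-label trial that already had 28 of its 80 patients in November 2020. It would have to be made without reference to outcome data.
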